### Participants

After pilot testing for reliability and validity of the measurement apparatus, recruitment of participants exclusively will take place in rural and urban primary and secondary schools with no restriction to school type. In South Africa, primary school attendees are aged 6–13/14 and secondary school children are between 13/14–18 years old, their German counterparts are 6–9/10 and 9/10–18. With approval from the German and South African supervisory school authorities, schools will be randomly selected per stratum (representing a combination of district and type of school) and contacted by the principal investigators. Schools (in blocks of five primary schools and five secondary schools) will be initially contacted via email and when interested visited by the study staff for further organisation. If the school wants to participate, consent forms for all pupils (and their parents) will be provided in the appropriate language (English, Afrikaans, Xhosa or German, Additional file 1). No limit will be set per school for maximum number of participating children per age. We will strive for an equal distribution of portion of participants per school to ensure equal representation. For participation, pupils will be requested to bring along the signed consent form on the testing day.

Inclusion criteria will consist of healthy children that are physically active for at least 120 accumulative minutes per week (parent reported). Children and young adolescents between the age of 6 and 18 will be recruited for this study. Exclusion criteria will be evaluated by parent proxy report and consist of current injuries of the lower extremity, abnormal gait or any neurological or neuromuscular abnormalities likely to influence the gait.

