### Sample size

Although we did not opt to distinguish primary or secondary outcome measures, the dAI was used to enable a sample size calculation. Muller et al. [36] has shown that the average dynamic arch index (μ: 0,19) and the accompanying standard deviation (SD: 0065) are stable between the ages of 6 and 13. The minimal important difference was set at 20 % of the average (0.19; i.e., 0.038). With a two-sided significance level of 0.05, and assuming a power of 0.8, a minimum of 16 participants per age group, per country, had to be included for this study. Due to the diversity of the study, additional power calculations have been performed. Based on the arch height ratio derived from Waseda et al. [22] the sample size for arch height ratio (navicular height*100/foot length) should be *n* = 12 per age group (μ = 15,0; SD = 2,6). Furthermore, based on a preliminary study on children, the sample size based on the standing long jump should be *n* = 18 (μ = 152,9; SD = 31,5), for lateral jumping *n* = 22 (μ = 38; SD = 9,2) and for 20 m sprint *n* = 12 (μ = 3,81; SD = 0,64). Therefore, our *n* = 20 per group seems to be sufficient. In order to allow for these differences and other unknown variances within the other variables we choose to increase the number from 16 to 20 participants per age group, per country.

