### Statistical analysis

Descriptive data will be presented using descriptive statistics. The participant’s barefoot questionnaire and the PAQ outcomes will be compared to all attending children in 2 primary (1 rural, 1 urban) and 2 secondary schools to assess external validity. The outcome measures will be evaluated for normality using Shapiro-Wilkins and visually using P-P plots, if possible, non-normal distributed data will be adjusted. Mixed Models linear regression will be used to assess if the foot mechanical and motor performance outcomes differ between the barefoot and the shod participants (fixed factors). Furthermore, we will test differences due to being barefoot or shod change by age by adding an interaction of age*group to the linear regression. Differences in foot strike pattern during jogging and sprinting between barefoot and shod participants will be assessed using ordinal regression. The school of a participant will be added to the model as a random effect in order to adjust for possible differences between the schools and their geographical location. Furthermore, Gender, BMI, PAQ-Score, ethnicity and inside/outside testing will be tested for confounding in all models (regression coefficient changes >10 %). We hypothesize that older boys could have higher arches (lower dAI) [37] and perform better on motor performance tasks, while girls’ feet will show a higher pliability. BMI increases the dAI and possibly decreases motor performance [38, 39]. A higher level of physical activity (higher PAQ score) is probably related to better motor performance. And lastly, Caucasians could have higher arches (lower dAI) [40].

We anticipate that gender might modify the effect of being barefoot or shod on the outcome measures and therefore gender will additionally tested as an effect modifier (interaction between outcome and gender *p* < 0.1). In all cases, a significance level of 5 % is pre-stipulated.

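### Per-age sample sizes treat children as independent although schools are sampled and modelled, so the stated 80% power per age group is not established; two of five listed outcomes miss it even without clustering

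*Protocol article*

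**What the plan says.** The Sample size section plans "With a two-sided significance level of 0.05, and assuming a power of 0.8". For the dynamic arch index (dAI), "The minimal important difference was set at 20 % of the average (0.19; i.e., 0.038"), which leads to "a minimum of 16 participants per age group, per country". It also lists 12 for arch height ratio, 18 for standing long jump, 22 for lateral jumping and 12 for the 20 m sprint. It then states "we choose to increase the number from 16 to 20 participants per age group, per country", giving as reasons the differences between outcomes and unknown variances, and judges 20 to be enough. With 13 ages and 2 countries, 13 × 2 × 20 = 520, the total in the abstract.

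Under Participants, schools are drawn at random within strata and approached in batches: "Schools (in blocks of five primary schools and five secondary schools"). All pupils of a participating school are offered consent. There is no cap on children per age within a school, although the team aims for even shares per school.

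Under Statistical analysis, "The school of a participant will be added to the model as a random effect". One mixed model is planned, with barefoot versus shod as the fixed factor and an age-by-group interaction. The article states no ICC, no final number of schools and no expected children per school.

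**The concern.** Children from one school tend to resemble each other in activity, facilities and testing conditions. The authors expect this, since they model school. Schools lie within country, so a country comparison at a given age compares sets of schools, and between-school variance adds to its error. The per-age sizes contain no such term, and the step from 16 to 20 is not explained by clustering.

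If the per-age power is taken at face value, a null result at a single age could be read as evidence of no difference when the comparison never had 80% power. Age-dependence is a stated aim, so readers will look at single ages.

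**Working it through.** **Inputs.** Two-sided 5%, 80% power and a difference of 20% of the mean. The article states the 20% rule for dAI only; applying it to the other outcomes is an assumption, supported by the three sizes that it reproduces. Means and SDs are those in Sample size; the dAI value, "standard deviation (SD: 0065"), is read as 0.065. The SDs are taken as total SDs.

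**Step 1: the plan's own figures.** For independent children, n per cell = 2(1.96 + 0.842)² / d² = 15.70 / d², with d = 0.2 × mean / SD. Power at 20 per cell is from the noncentral t with 38 df.

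| Outcome | d | n, normal / t | Stated n | Power at 20 |
|---|---|---|---|---|
| Arch height ratio | 3.0/2.6 = 1.154 | 12 / 13 | 12 | 94–95% |
| 20 m sprint | 0.762/0.64 = 1.191 | 12 / 13 | 12 | 96% |
| Standing long jump | 30.58/31.5 = 0.971 | 17 / 18 | 18 | 85% |
| Lateral jumping | 7.6/9.2 = 0.826 | 24 / 25 | 22 | 72% |
| dAI | 0.038/0.065 = 0.585 | 46 / 47 | 16 | 44% |

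Arch height, sprint and long jump reproduce with no room for a design effect. Lateral jumping is close to its stated 22, but 22 already exceeds 20. The dAI figure does not reproduce: 15.70 / 0.585² ≈ 46. One-sided and one-sample variants do not give 16 either.

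**Step 2: clustering.** Design effect D = 1 + (m − 1) × ICC, where m is children per school at one age. The noncentrality is d × √(20 / (2D)). Both m and ICC are assumptions. Ranges run from school-level df (2 × schools per country − 2) to child-level df (38).

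| | ICC 0.05 | ICC 0.10 | ICC 0.20 |
|---|---|---|---|
| Long jump, m = 4 (5 schools) | 71–80% | 66–75% | 57–66% |
| Long jump, m = 2 (10 schools) | 81–83% | 79–81% | 76–78% |
| Lateral jumping, m = 4 | 57–66% | 52–61% | 44–52% |
| Arch height, m = 4 | 85–91% | 80–88% | 72–80% |
| Sprint, m = 4 | 87–93% | 82–90% | 74–83% |

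Example: long jump, m = 4, ICC 0.10. D = 1.30, effective n = 20/1.30 = 15.4, noncentrality = 0.971 × √(15.4/2) = 2.69, power 75% with 38 df. With m = 10 (2 schools per cell) and 38 df, long jump is 70% at ICC 0.05 and 58% at 0.10.

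**Step 3: break-even for long jump.** The normal approximation reaches 80% at D = 1.20, so ICC = 0.20/3 = 0.067 for m = 4. With 38 df, D = 1.15 (ICC 0.05) already gives 79.7%. The threshold is therefore about 1.15 to 1.2.

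**Step 4: pooled over ages.** Assume 260 children per country in 10 schools of 26, ICC 0.10 and 18 df. D = 1 + 25 × 0.10 = 3.5 and effective n = 260/3.5 = 74 per country. Power is at least 92% for every listed outcome, dAI being the lowest.

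**The case against.** Much of the case on the other side stands.

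- **The planned analysis is one model over all ages, with no separate test per age.** This is right, and a reader might infer from Step 2 that the main group comparison is underpowered. The documents do not support that. Pooled power is high under moderate clustering. If age enters linearly with an age-by-group term, the long jump difference at any given age has about 93% power at ICC 0.10, assuming 5 primary and 5 secondary schools per country. The per-age figures matter only because Sample size states its power that way.
- **Nothing shows that long jump falls below 80%.** This is also right. It has a margin at 20 per cell, and the article gives neither ICC nor cluster size. A breach is possible but not demonstrated.
- **Five schools per country is not in the plan.** The batches of five describe how schools are contacted, not how many enrol. The aim of even shares per school works against heavy concentration.
- **The low ends of the ranges are not all due to correlation.** With 8 df and ICC 0, long jump is already 76.7%, so more than half of the drop from 85% to 71% comes from the df.
- **Exposure is classified per child by the barefoot questionnaire.** It would be too strong to call the barefoot-versus-shod contrast wholly between schools. That description fits the per-country cells of the sample size.

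What remains is that a stated power figure leaves out a variance component that the same article puts in its model. This concerns a printed claim, not a detail left to a fuller document.

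**Conclusion.** The point holds in a limited form. The per-age, per-country sizes rest on independence, while sampling and analysis are by school, so any positive ICC lowers per-age power below the independence figure.

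How far depends on unstated quantities. Long jump goes from about 85% to below 80% once the design effect passes roughly 1.15 to 1.2, that is, ICC about 0.05 to 0.07 with an assumed four children per school and age. With two per school it stays near 80% up to ICC 0.10. Arch height and sprint hold at about 80% or more up to ICC 0.10 with four per school.

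The larger faults in the same paragraph do not depend on clustering: dAI needs about 46 per cell rather than 16 and has about 44% power at 20, and lateral jumping has 72%. The pooled comparison is well powered under moderate clustering. Its weakest case is dAI with few schools: about 77% (normal approximation) with 5 schools of 52 per country at ICC 0.10.

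**What to change.** Keep enrolment at 520 and revise the Sample size section as follows:

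1. Correct the dAI figure, or correct the inputs if one was misprinted.
2. Report per-age power at 20 per cell for each listed outcome, using 1 + (m − 1) × ICC over a stated range, for example ICC 0.05 to 0.20 and two to four children per school and age, and say which df are used.
3. Replace the conclusion that 20 per group is enough with what those figures show, including that dAI and lateral jumping fall short per age.
4. State that the 80% target applies to the comparison pooled over ages in the mixed model, and report age-specific differences as estimates with confidence intervals.

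The cost is a short recalculation and some rewording, with no added participants. The per-age power statement becomes less favourable.

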### Testing procedure

Methodological planning stipulates all anthropometrical, foot and motor performance measurements to be performed during a physical education lesson. Prior to the testing, a physical activity questionnaire for children/adolescent (PAQ-C and PAQ-A [25, 26]) and a barefoot questionnaire will be distributed by the teachers and collected by the study staff on the testing day and briefly checked for completeness. All children bringing the signed consent form and voluntarily want to participate will be gathered and all relevant information for the testing will be given by the principal investigator. After a short warm up period (jogging for < 5 min), participants will be randomly allocated to the seven testing stations:AnthropemetryFoot caliperPressure plate20 m sprintingLateral jumpingStanding long jumpBackwards balancing

After their first testing station, a participant will be transferred to the next vacant station without a fixed order. Testing station 1–3 will be completed only barefoot, while testing stations 4–7 will be performed in barefoot and shod conditions. The order of the condition is randomized a priori on the registration sheet which is distributed to the participants on the testing day. A flowchart displaying the participant flow through the study is shown in Fig. 1.

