### Barefoot questionnaire

In designing the study, decisions have been made that could influence the outcome and its interpretations. The level of barefootness of the participants in South Africa is one of those decisions since the current literature descriptions are diverse and even ambiguous at times.

Some studies use a percentage of yearly mileage [8, 9] or running time [41] to define a habitually barefoot person. Other studies define a habitually barefoot individual as being barefoot for all life [8, 14, 16, 20] or as living in an area where it is common to be barefoot [15, 19, 21]. Children in Germany are shod most of the time due to the climate and the culture of wearing shoes when outside. In South Africa a culture exists for children of being barefoot outside, and for younger children, even during sports and at school. Furthermore, the warmer climate allows the children to do so for the biggest part of the year. To distinguish between children who are habitually barefoot, a barefoot questionnaire has been developed. Participants in primary school (age range 6–12 years) are defined as habitually barefoot when they are always barefoot in and around the house as well as at school or during sports when it is warm. In secondary school being habitually barefoot is defined as always being barefoot in and around the house and having had the level of barefootness at primary school as previously described. The distinction between primary and secondary school was made because all secondary schools require wearing a uniform that includes wearing shoes and participation in most sports do as well. Therefore, it wasn’t feasible to include participants after the age of 13 years who had a similar level of barefootness as their counterparts in primary school.

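### The quota of 20 per age is counted by country, but the analysis compares questionnaire-defined barefoot and shod children, so nothing secures 20 barefoot children per age

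*Protocol article*

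**What the plan says.** **Counting unit.** The Sample size section gives "assuming a power of 0.8, a minimum of 16 participants per age group, per country, had to be included for this study" and then raises this: "we choose to increase the number from 16 to 20 participants per age group, per country". The same section also speaks of 20 per group without saying whether a group is a country or an exposure class. The Abstract's total of 520 fits the country reading: 13 one-year ages × 2 countries × 20.

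**Analysed unit.** Under Statistical analysis, mixed models assess whether outcomes "differ between the barefoot and the shod participants (fixed factors". An age-by-group term is then added to the same model. Country is not the factor.

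**How a child gets a group.** Under Barefoot questionnaire (Methods), a six-item form decides. Primary pupils count as barefoot if always barefoot at home and always barefoot at school or in sports in warm weather. Secondary pupils must have had that level in primary school and be always barefoot at home now.

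**Entry.** The Participants section asks for age, health, weekly activity and absence of injury or gait problems. It has no barefoot criterion. Under Testing procedure, "a barefoot questionnaire will be distributed by the teachers and collected by the study staff on the testing day", where it is checked for completeness; no classification before a child counts toward the quota is mentioned.

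**The concern.** A South African child who does not meet the questionnaire rule fills one of the 20 South African places but not a barefoot place. The text does not say whether that child then counts as shod or drops out of the comparison. A team that follows the plan exactly can reach 520 children and still have too few barefoot children at some ages, in unknown and uneven numbers.

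The sample size is worked out per age group, and age dependence of the barefoot–shod difference is a stated aim. Thin barefoot cells would therefore weaken the part of the study that the per-age sizing is meant to support, and they cannot be refilled once testing has ended.

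**Working it through.** **Inputs (Sample size section).** "With a two-sided significance level of 0.05, and assuming a power of 0.8". For the dynamic arch index (dAI): "The minimal important difference was set at 20 % of the average (0.19; i.e., 0.038"; "the accompanying standard deviation (SD: 0065) are stable between the ages of 6 and 13". The SD is read as 0.065, on the assumption that the decimal mark was lost. Other outcomes (mean; SD; stated n): arch height ratio 15.0; 2.6; 12. Long jump 152.9; 31.5; 18. Lateral jumping 38; 9.2; 22. Sprint 3.81; 0.64; 12. The 20% rule is stated only for dAI; applying it to the others is an assumption, tested in step 1.

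**1. The plan's own figures.** Two groups, normal approximation: n per group = 2(1.960 + 0.842)² × (SD/Δ)² = 15.70 × (SD/Δ)², with Δ = 20% of the mean.

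| Outcome | Δ | (SD/Δ)² | n per group | Stated |
|---|---|---|---|---|
| Arch height ratio | 3.00 | 0.751 | 11.8 → 12 | 12 |
| Long jump | 30.58 | 1.061 | 16.7 → 17 | 18 |
| Lateral jumping | 7.6 | 1.465 | 23.003 → 24 | 22 |
| Sprint | 0.762 | 0.705 | 11.1 → 12 | 12 |
| dAI | 0.038 | 2.926 | 45.9 → 46 | 16 |

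Four of the five agree within 2, so the section describes a two-group comparison within one age group. The dAI figure of 16 does not reproduce; it would need an SD of about 0.038.

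**2. Cell sizes.** Let f be the share of South African children meeting the rule, with all German children taken as shod. Barefoot children per age = 20f. Shod children per age = 40 − 20f if the rest count as shod, or 20 if they are left out. For f = 0.75 this is 15 v 25 or 15 v 20. For f = 0.5 it is 10 v 30 or 10 v 20.

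**3. Power within one age.** Two-sided t-test at 0.05, noncentrality (Δ/SD)/√(1/n₁ + 1/n₂), n₁ + n₂ − 2 degrees of freedom.

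| Outcome | 20 v 20 | 15 v 25 | 10 v 30 | 15 v 20 | 10 v 20 |
|---|---|---|---|---|---|
| Long jump | 0.85 | 0.83 | 0.74 | 0.79 | 0.68 |
| Lateral jumping | 0.72 | 0.69 | 0.60 | 0.65 | 0.54 |
| dAI | 0.44 | 0.41 | 0.35 | 0.38 | 0.31 |
| Sprint | 0.96 | 0.94 | 0.89 | 0.92 | 0.84 |
| Arch height ratio | 0.94 | 0.93 | 0.87 | 0.91 | 0.82 |

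**4. Age-by-group slope.** With age linear and the same f at every age, the standard error relative to 20 v 20 is √[(1/n₁ + 1/n₂)/(1/20 + 1/20)].
- 15 v 25: √(0.1067/0.1) = 1.03
- 10 v 30: √(0.1333/0.1) = 1.15
- 15 v 20: √(0.1167/0.1) = 1.08
- 10 v 20: √(0.15/0.1) = 1.22

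If only ages 13–18 lose half their barefoot children, the rise is about 7% (rest counted as shod) or 11% (left out).

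**5. Pooled main effect, dAI, f = 0.5.** Noncentrality is 0.5846/√(1/130 + 1/390) = 5.77, or 0.5846/√(1/130 + 1/260) = 5.44. Power exceeds 0.999 in both cases.

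Steps 3 to 5 ignore covariates and school clustering.

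**The case against.** **No shortfall is shown.** A reader might infer that the barefoot cells will fall below 20. The documents do not support that. They give no barefoot share. Study design says the barefoot habit prevails in South Africa, 16 is called a minimum, and no cap is set per school. The Discussion's remark on which pupils over 13 it was feasible to include can be read as selection on barefoot status. None of this is a criterion or a counting rule, however. What stands is that cells may fall short and nothing prevents it.

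**The secondary-school shoe rule.** It is tempting to read "all secondary schools require wearing a uniform that includes wearing shoes" as the reason losses would concentrate at the older ages. In the Discussion that sentence explains why the definition was relaxed for those pupils. Wearing shoes at secondary school disqualifies nobody. Losses at those ages are possible, because two conditions must still be met, but this requirement is not evidence for them.

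**The model pools ages.** No separate test per age is planned, so the per-age powers do not describe the main analysis, and the pooled effect hardly moves. This stands, and it limits the damage to age-specific contrasts and the age-by-group term. The per-age cell is still the unit in which the protocol justifies its own sample size.

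**Other faults weigh more for some outcomes.** This also stands. dAI and lateral jumping are below 0.8 at 20 v 20, before any child is reclassified, while sprint and arch height ratio stay above 0.8 in every case above.

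**Conclusion.** The mismatch holds: children are counted by country, compared by questionnaire class, and no rule links the two. The stated per-age sample size is therefore not secured for the barefoot–shod contrast.

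The consequence is moderate and conditional. At an assumed 75% share it is small: long jump 0.83 instead of 0.85, and a slope standard error 3% larger (8% if the remaining children are dropped). At 50% it is material: long jump 0.74, and 15% or 22%. The pooled main effect is not at risk from reclassification alone.

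These figures rest on the assumed shares, the 20% difference for every outcome, German children all being shod, linear age for the slope, and no allowance for clustering or covariates. The low per-age power for dAI and lateral jumping exists at 20 v 20 and must not be attributed to this mismatch.

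**What to change.** Preferred: state the quota by exposure, as 20 questionnaire-classified barefoot and 20 questionnaire-classified shod children per age year. Classify each child from the form already collected on the testing day before counting the child toward a cell. State whether South African children who do not meet the barefoot rule count as shod or are left out. The cost is a changed counting rule at registration and some extra children screened. To reach 20 barefoot children per age, about 20/0.75 = 27 South African children are needed at a 75% share and 20/0.5 = 40 at 50%.

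Alternative: keep 20 per country, give the expected share meeting the rule separately for primary and secondary ages, and restate the power for the resulting cells. This changes wording only.

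Either way, define what 20 per group refers to, and restate the dAI and lateral jumping figures. With the stated inputs a 20 + 20 quota gives per-age power of 0.44 (SD read as 0.065) and 0.72, not 0.8.
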